### Sample size

A four-armed randomized controlled pilot trial was recently conducted by the authors. A total of 76 community-dwelling older adults with symptoms of sleep disturbance took part in the pilot trial, with an attrition rate of 30%. They were randomly assigned to four different groups, including a MBI group, a TCC group, a MBTCC group, and a SHE group. The results of this pilot study are summarized in Table 1. Although the pilot study yielded moderate to large effect sizes (between .42 and .78), this variation implies that the effect sizes might be sample-dependent or context-dependent. In the current study, a larger sample size is therefore considered to be more desirable because it could pave the way for the identification of a small and hidden effect. Hence, in this power analysis, the effect size is set to .25 and the alpha level is .05. It is suggested that, to obtain the power level of .86 for the main effect and .97 for the interaction effect, at least 180 total participants are needed. Given that this study is longitudinal in nature and attrition (assuming the rate is 30%) is likely, an additional 76 participants will be recruited, resulting in a total of 256 participants (64 per arm).

**Table 1 Tab1:** Comparison between four study arms in a pilot study

Variable	MBI group (*n* = 22)		TCC group (*n* = 23)		MBTCC group (*n* = 10)		SHE group (*n* = 21)		Effect size (MBI vs SHE), Cohen’s *d*	Effect size (TCC vs SHE), Cohen’s *d*	Effect size (MBTCC vs SHE), Cohen’s *d*	Effect Size (MBI vs TCC), Cohen’s *d*
	Pre, mean (SD)	Post, mean (SD)	Pre, mean (SD)	Post, mean (SD)	Pre, mean (SD)	Post, mean (SD)	Pre, mean (SD)	Post, mean (SD)				
ISI	17.27 (3.69)	15.64 (3.44)	17.22 (3.59)	15.70 (3.21)	17.10 (3.35)	14.40 (3.10)	16.95 (3.28)	16.90 (3.55)	− 0.44	− 0.42	− 0.78	− 0.03
SF12 (Phy)	11.05 (2.75)	11.55 (2.06)	11.48 (2.88)	12.91 (2.91)	11.90 (2.60)	13.90 (2.23)	12.76 (3.39)	12.52 (3.27)	0.24	0.52	0.69	− 0.32
SF12 (Men)	16.18 (3.66)	18.05 (3.75)	16.09 (3.40)	16.96 (3.05)	17.40 (3.20)	19.50 (3.21)	17.67 (3.90)	17.95 (3.50)	0.41	0.16	0.48	0.28
RRQ	3.06 (.79)	2.61 (.77)	2.89 (.88)	2.79 (.78)	3.23 (1.03)	2.68 (.84)	3.13 (.83)	3.10 (.66)	− 0.51	− 0.08	− 0.57	− 0.41
HS	62.23 (6.75)	57.59 (6.29)	61.39 (6.89)	53.52 (6.90)	64.00 (5.94)	54.70 (6.93)	63.29 (5.88)	61.48 (6.77)	− 0.44	− 0.93	− 1.24	0.47

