#### Intervention and assessment fidelity

Each group will be taught by two qualified instructors and each session will be conducted in a similar amount of contact time. Each programme will consist of eight weekly sessions of 2 to 3 h each (16 to 24 h in total). There will be eight to 12 participants in each group. To ensure the fidelity of the intervention, qualified therapists with basic professional training in the teaching of mindfulness-based interventions, in addition to at least 2 years of experience conducting mindfulness-based programmes, will be invited to teach the MBTCC and MBI groups. Experienced Tai Chi masters will be invited to implement the MBTCC and TCC groups. The invited Tai Chi masters should have at least 10 years of experience of practice and teaching TCC. Experienced occupational therapists with at least 10 years of experience conducting mental health psychoeducation programmes will be invited to implement the SHE control group. The fidelity of each intervention programme will be ensured and monitored by a random review of two out of eight sessions. Based on the programme content of the respective intervention programmes, fidelity checks will be independently conducted by an experienced mindfulness instructor, an experienced Tai Chi master, or an experienced occupational therapist. For the qualitative part of the research project, the research personnel will receive half a day of training to learn the corresponding interview questions and the process for conducting the focus groups. In addition, regarding the qualitative analysis, another team of independent raters will audiotape, transcribe, and review the contents of the qualitative interviews to identify corresponding themes.

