### Data processing and analysis

The data will be analysed using SPSS version 26.0 on an intention-to-treat basis. To test the first study hypothesis, we will employ linear mixed models with restricted maximum likelihood estimation to test the individual growth model. This integrated random coefficient approach is usually conceptualized as a two-level model. Level 1, or the within-subject model, is the model used for repeated measures. Level 2, or the between-subjects model, is the model used for time-invariant variables between groups of individuals. The time factor, the grouping factor, and the interaction effect in mixed modelling will be examined. Additionally, the trend depicted in the least square mean plot will be evaluated to determine whether or not any trend-based differences exist between different groups. Hypothesis 1 would be supported if the models assessed and compared are fitted by using appropriate fit statistics. To test hypotheses 2 to 4, macro PROCESS SPSS and the bootstrapping approach will be used to assess the moderated mediation effects in the path model. Each mediator will be mean centred to form the interaction terms. The effects of covariates such as age or gender will be adjusted accordingly. The PROCESS macro is based on ordinary least squares regression. In addition, the mediating effect will be examined by data visualization techniques, such as Trellis coplot, also known as the conditional plot. Hypotheses 2 to 4 would be supported if any mediation effect exists.

The contents of the focus group interviews will be audiotaped and transcribed by a team of independent raters. Thematic analysis will be conducted with the help of the software NVivo (version 12) to store and manage the data. Coding and analysis will involve interpretative phenomenological analysis, which uses a bottom-up approach to determine the themes. Throughout the analysis, the codes will be identified from frequently used words or ideas in the transcripts. The codes will then be categorized into larger recurrent themes for further analysis. The research team will meet to discuss the significance of each theme and to triangulate the results with the quantitative findings.

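### All four arms are taught in classes of 8 to 12, but the Hypothesis 1 model has no class level and the power has no design effect, so standard errors are too small and power too high for any positive class correlation

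*Protocol article*

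**What the plan says.** The Participants section randomises individuals to arms after the baseline assessment. Under Intervention and assessment fidelity, delivery is in classes in every arm: "Each group will be taught by two qualified instructors and each session will be conducted in a similar amount of contact time" and "There will be eight to 12 participants in each group". Group must mean a class here, because an arm has 64 people. Each programme runs weekly for eight sessions, 16 to 24 hours of shared contact in all, and the control programme follows the same pattern.

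The Data processing and analysis section describes the Hypothesis 1 model thus: "This integrated random coefficient approach is usually conceptualized as a two-level model". It then defines the levels: "Level 1, or the within-subject model, is the model used for repeated measures", and "Level 2, or the between-subjects model, is the model used for time-invariant variables between groups of individuals". The terms follow: "The time factor, the grouping factor, and the interaction effect in mixed modelling will be examined". No class or instructor term and no cluster-robust variance is named. Hypotheses 2 to 4 use a macro that the section says rests on ordinary least squares.

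The Sample size section takes an effect size of .25 and alpha of .05, and states power of .86 for the main effect and .97 for the interaction, for which "at least 180 total participants are needed". It adds 30% for attrition to reach 256. It contains no ICC and no design effect.

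**The concern.** People who spend eight weeks in the same room with the same teachers and classmates tend to have correlated outcomes afterwards. Individual randomisation does not prevent this, because the correlation arises after randomisation, through shared delivery. It enters at T2, T3 and T4, the visits at which Hypothesis 1 compares the arms. A person-level random coefficient models correlation between visits of one person; it cannot absorb variance between classes.

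If class is left out, classmates are counted as independent, confidence intervals for the arm contrasts are too narrow, and the type I error exceeds its nominal level. A few unusually good or poor classes in one arm could then be read as a treatment effect. The least-squares mediation models share the independence assumption. The planned sample size also promises more power than a trial with clustered delivery would have.

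**Working it through.** **Inputs from the protocol.** 64 per arm; classes of 8 to 12; 180 analysed; 30% attrition; alpha .05; stated powers .86 (main effect) and .97 (interaction); four arms, four visits.

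**Assumptions.** The class ICC is not given; 0.01 to 0.10 is assumed. Tests are taken as two-sided and .25 as Cohen's f, since the protocol states neither.

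**The plan's own figures.** Enrolment: 180/(1 − 0.30) = 257.1, so 258 after rounding up, against 256 stated; this agrees closely enough. Power: a one-way F test of four arms with N = 180 and f = .25 has noncentrality 180 × 0.0625 = 11.25 and power .80, not .86. A repeated-measures calculation gives .86 only with an unstated correlation between visits of about 0.83, and the interaction power then exceeds .99. No single set of inputs tried gave both stated powers. The test, the correlation and the effect-size metric are not stated, so .86 and .97 are taken as given below and are not called wrong.

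**Number of classes.** 64/8 = 8 and 64/12 = 5.3, so at least 6. That is 6 to 8 per arm and 24 to 32 in all.

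**Class size in the analysis.** For a typical class of 10, 10 × 0.70 = 7 remain after attrition. Both 7 and 10 are shown.

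**Formulas.**
- Design effect: DE = 1 + (m − 1) × ICC.
- Actual size of a nominal 5% test: 2 × [1 − Φ(1.96/√DE)].
- Power: find the noncentrality that gives the stated power, divide it by DE, and recompute. For .86 with 3 and 176 degrees of freedom it is 12.91; for .97 with 9 and 528 it is 26.60.

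**Example** (m = 7, ICC 0.05). DE = 1 + 6 × 0.05 = 1.30. Size: 1.96/√1.30 = 1.719, giving 0.086. Main effect: 12.91/1.30 = 9.93, power .75. Interaction: 26.60/1.30 = 20.46, power .905.

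| Analysed per class | ICC | DE | Actual size | Interaction (.97 stated) | Main effect (.86 stated) |
|---|---|---|---|---|---|
| 7 | 0.01 | 1.06 | 0.057 | .96 | .84 |
| 7 | 0.05 | 1.30 | 0.086 | .905 | .75 |
| 7 | 0.10 | 1.60 | 0.121 | .82 | .65 |
| 10 | 0.01 | 1.09 | 0.060 | .95 | .83 |
| 10 | 0.05 | 1.45 | 0.104 | .86 | .70 |
| 10 | 0.10 | 1.90 | 0.155 | .735 | .57 |

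**Two qualifications.** The interaction column is closest to Hypothesis 1, which is about greater improvement at T2 to T4. The main-effect column overstates the loss due to the design effect: the full DE is applied to all four visits, although T1 precedes the classes and is not clustered. In the other direction, the table keeps person-level degrees of freedom. With 24 to 32 classes and four arms, the arm test has only about 24 − 4 = 20 to 32 − 4 = 28 denominator degrees of freedom, which lowers power further.

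**The case against.** **The model may not be fully fixed.** The two-level sentence reads as a general remark on growth models. The article gives no full list of random effects and no method for degrees of freedom, and it says a full protocol is available on request. A class effect could be specified there. This stands as a limit on certainty. But the article goes on to define what each level holds and which terms are examined, and class has no place among them. An analysis that follows this text would omit it.

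**The size is assumed.** This also stands. At an ICC of 0.01 the actual size is 0.057 to 0.060, which is minor. Nothing in the protocol supports a particular value, and the larger figures need an ICC of 0.05 or more.

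**The power for Hypothesis 1 may remain adequate.** With 7 analysed per class, the approximation keeps the interaction power above .80 over the whole assumed range, before the loss from fewer degrees of freedom. This tempers the power point, not the type I error point.

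**Stronger readings that a reader might infer.**
- That the information on an arm difference is just the number of classes. This is so only as the ICC approaches 1. At ICC 0.05 with 7 per class, the effective number is 180/1.30 = 138, far above 24 to 32. The class count limits the degrees of freedom, not all of the information.
- That the three recruiting centres add to the inflation. Individuals are randomised, so existing differences between centres balance across arms in expectation.
- That shared teachers must raise the class ICC. The protocol requires two instructors per class but does not say whether the pairs differ between classes. If one pair taught all of an arm's classes, it would add nothing to the variation between classes within that arm.

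**Conclusion.** The concern holds. Delivery is clustered in all four arms, the model as described has no class level, the mediation models assume independent people, and the power makes no allowance. The direction of the error follows for any positive class ICC.

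The size is conditional on that ICC. Over an assumed 0.01 to 0.10, the actual size of a nominal 5% test is about 0.057 to 0.121 with 7 analysed per class and 0.060 to 0.155 with 10. The stated .97 becomes about .96 to .82, or .95 to .735. The stated .86 becomes at worst, by the design effect alone, about .84 to .65, or .83 to .57. The effect is small at the bottom of the range and material from about 0.05 upwards. These are approximations, and the powers start from stated figures that could not be reproduced. The documents do not support saying that the primary inference is certainly invalid, or that .86 falls to one particular value.

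**What to change.** - **Data.** Record class identity prospectively for every participant in every arm.
- **Hypothesis 1 model.** Add to the Insomnia Severity Index mixed model a random class effect, nested in arm and acting on T2 to T4 through a post-baseline indicator, with Satterthwaite degrees of freedom. Replace the two-level description with visits within participants within classes.
- **Mediation.** Account for class in Hypotheses 2 to 4, for example by a multilevel mediation model or as a sensitivity analysis. A bootstrap that resamples whole classes is fragile with 6 to 8 per arm and should not be the only safeguard.
- **Power.** Restate both .86 and .97 with a design effect over a stated ICC range, and say which test, correlation and effect-size metric they rest on.

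**Cost.** One more recorded variable, a post-baseline indicator and an additional random effect in the model. Intervals become wider and the stated power less favourable, noticeably so if the ICC is 0.05 or more. If the ICC proves negligible, the point estimates should barely change.

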### Hypotheses

Hypothesis 1. Participants in the MBTCC group will report significantly greater improvements at 8-week (T2), 6-month (T3), and 12-month (T4) follow-ups in regard to measures of the primary outcome of insomnia severity, compared with participants in the MBI-alone group, the TCC-alone group, and the SHE control group.Hypothesis 2. Participants in the MBI-alone group will experience significantly greater improvements than those in the SHE control group in the primary outcomes across time, in which the beneficial effects on insomnia severity will be mediated by rumination and psychological function.Hypothesis 3. Participants in the TCC-alone group will experience significantly greater improvements than those in the SHE control group in the primary outcomes across time, in which the promising effects on insomnia severity will be mediated by the arousal level and physical function.Hypothesis 4. The favourable effects of the MBTCC group on insomnia severity will be mediated by all the proposed mediators.

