### Study design

Because both quantitative and qualitative data will be collected, this study has a sequential explanatory design. This is a superiority trial, with equal allocation to the intervention and control groups. Specifically, qualitative data will be collected after the quantitative phase is finished, and qualitative data with rich contexts will be used to illuminate the quantitative findings. The current quantitative study is a randomized controlled trial with four study arms: (1) a MBTCC group, (2) a MBI group, (3) a TCC group, and (4) a SHE control group. The outcome measures will be collected at four time points: at baseline (T1), after the 8-week intervention (T2), 6 months after the intervention (T3), and 1 year after the intervention (T4). In addition, qualitative evaluation through focus group interviews will be conducted at the end of the 12-month assessment period (T4). The study flowchart is displayed in Fig. 2.

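### The stated success criterion for Hypothesis 1 is model fit, which does not test whether MBTCC is better than MBI, TCC and SHE

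*Protocol article*

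**What the plan says.** **The hypothesis.** Under Hypotheses, the first hypothesis reads "Participants in the MBTCC group will report significantly greater improvements at 8-week (T2), 6-month (T3), and 12-month (T4) follow-ups" on insomnia severity, "compared with participants in the MBI-alone group, the TCC-alone group, and the SHE control group". That is three comparators at three visits, with MBTCC the better arm each time. Study design adds: "This is a superiority trial, with equal allocation to the intervention and control groups".

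**The analysis.** Data processing and analysis says "we will employ linear mixed models with restricted maximum likelihood estimation to test the individual growth model". It continues: "The time factor, the grouping factor, and the interaction effect in mixed modelling will be examined". It also says that "the trend depicted in the least square mean plot will be evaluated to determine whether or not any trend-based differences exist between different groups".

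**The criterion.** The same section then states when the hypothesis counts as confirmed: "Hypothesis 1 would be supported if the models assessed and compared are fitted by using appropriate fit statistics". No other part of the article replaces this sentence.

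**The concern.** Fit statistics rank models or describe how closely a model follows the data. They carry no sign and name no arm. A model with group and group-by-time terms can fit better because MBI and TCC both beat SHE while MBTCC adds nothing to either. It can also fit better because MBTCC does worse than the others. If the sentence means only that the fitted model is adequate, it can be met whatever the arms do.

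This is the decision rule for the primary hypothesis of a superiority trial. The trial's purpose is to learn whether the combination outperforms its components, and the written rule does not ask that question. It is a rule that is stated and does not match its hypothesis, which is different from a detail left to a later analysis plan.

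**Working it through.** **1. Hypothesis and rule side by side.**

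| Element | Hypothesis 1 | Stated criterion |
|---|---|---|
| Arms compared | MBTCC vs MBI, vs TCC, vs SHE | none named |
| Direction | MBTCC better | none |
| Visits | T2, T3 and T4 | none named |
| Contrasts | 3 × 3 = 9, joined by 'and' | none |
| Evidence | significant difference | fit statistic, not named |

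Nothing in the right-hand column can confirm or refute the left.

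**2. The plan's own figures.** Sample size gives 180 evaluable participants and 30% attrition. 180 / 0.70 = 257.1, rounded up to 258, against the stated 256 (256 × 0.70 = 179.2), so the total is reproduced to within two participants. The power calculation states that "the effect size is set to .25 and the alpha level is .05", with power .86 for the main effect and .97 for the interaction. These are powers of omnibus tests. None is given for the nine contrasts, and the point below does not depend on them.

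**3. How often a fit rule could mislead.** The article gives no figure for this, so it was simulated. From the documents: four arms, four assessments, 64 per arm randomised, 45 per arm evaluable (180 / 4), and pilot ISI effects against SHE of 0.44 (MBI) and 0.42 (TCC) from Table 1. Assumed: random intercept with correlation 0.5 between assessments, effects in SD units that last from T2 to T4, complete data, time as categories, and 2,000 trials per setting.

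The comparison is a group-by-time model against a time-only model, both fitted by maximum likelihood. The extra parameters number 16 − 4 = 12. With D as twice the log-likelihood difference, the larger model is preferred when:
- AIC: D > 2 × 12 = 24
- likelihood-ratio test at 0.05: D > 21.0
- BIC: D > 12 × ln(N), which is 62.3 at N = 180 and 66.5 at N = 256

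Hypothesis 1 as worded was checked in the same trials by requiring z > 1.96 in favour of MBTCC for all nine differences in change from baseline.

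| Scenario (effects vs SHE) | n per arm | AIC | LRT | BIC | All nine contrasts |
|---|---|---|---|---|---|
| (a) MBI 0.44, TCC 0.42, MBTCC 0.43 | 45 | 60% | 74% | 0.1% | 0.0% |
| | 64 | 80% | 88% | 0.4% | 0.0% |
| (b) MBI 0.44, TCC 0.42, MBTCC 0 | 45 | 80% | 88% | 0.4% | 0.0% |
| | 64 | 94% | 97% | 1.9% | 0.0% |
| (c) all arms equal | 45 | 2.4% | 5.7% | 0% | 0.0% |
| | 64 | 2.5% | 6.0% | 0% | 0.0% |

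In (a) MBTCC is no better than its components, and in (b) it is no better than SHE, so Hypothesis 1 is false in both. A second run with a different random seed agreed to within about two percentage points.

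**4. What a matching rule would demand.** With the pilot effects taken as true (0.44, 0.42 and 0.78 for MBTCC), MBTCC exceeds MBI by 0.78 − 0.44 = 0.34 and TCC by 0.78 − 0.42 = 0.36. Under the same assumptions, all nine contrasts succeeded in 5.2% of trials at 45 per arm and 11.9% at 64 per arm. These use unadjusted change scores, and the pilot MBTCC arm had only 10 participants, so they show the order of magnitude only.

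**The case against.** The strongest reply is that the section also examines the time, group and interaction effects and looks at group trends in the least-squares means, while the hypothesis itself asks for significant differences. On that view the sentence is clumsy drafting, and a reader might wrongly infer that the investigators mean to declare success whatever MBTCC does. The documents do not show such an intent, and the reply stands to that extent. It does not repair the rule: those effects are not made the criterion, and an omnibus group or interaction test has no direction and does not compare MBTCC with each of the three arms.

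Three stronger readings are tempting but not supported.
- **Any one of the nine contrasts counts as success.** At two-sided 0.05 that would give about a 13% to 16% chance of at least one false favourable result. No such rule is written, and the hypothesis joins comparators and visits with 'and'.
- **The use of REML makes the fit comparison invalid.** That holds only if models with different fixed effects are compared by REML likelihood. The article does not say which models are compared, and REML is suitable when only the covariance structure differs.
- **The missing contrast list and multiplicity rule are faults in themselves.** An article may leave these to the full protocol or analysis plan. Only the sentence that is stated, and does not fit its hypothesis, is at issue.

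**Conclusion.** The criterion for Hypothesis 1 does not test Hypothesis 1 and must be restated. This follows from the text alone and needs no assumption.

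The size of the consequence does rest on assumptions. Where MBI and TCC work at pilot size and MBTCC adds nothing over them or over SHE, a fit rule would point to support in under 2% of trials with BIC and in about 60% to 97% with AIC or a likelihood-ratio test. With all arms equal the range is 0% to about 6%. These figures depend on the assumed correlation of 0.5, lasting effects, complete data, and reading the fit comparison as one with and without group terms. The article fixes none of these readings, and its silence on the fit statistic is why the range is so wide.

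**What to change.** Replace the sentence with a rule along these lines: *From the mixed model, the MBTCC−MBI, MBTCC−TCC and MBTCC−SHE differences in ISI change from baseline will be estimated at T2, T3 and T4 with 95% confidence intervals. Hypothesis 1 is supported only if all nine differences favour MBTCC at two-sided 0.05. Fit statistics will be used only to choose the covariance or growth form, with maximum likelihood instead of REML whenever the compared models differ in fixed effects.*

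Because every contrast must succeed, this joint claim needs no split of alpha. If the investigators prefer to claim visits or comparators separately, that is a different hypothesis, and a multiplicity rule must be set before the data are seen.

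The change costs wording only: no new data and no new model. Its price is in expectations. The powers of .86 and .97 under Sample size do not carry over, and the chance of meeting the joint rule is lower. The investigators should state power for the rule they adopt.

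### Hypotheses 2 to 4 claim mediation, but the plan tests moderated mediation with no named moderator and accepts any mediation effect, even where hypothesis 4 needs all mediators

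*Protocol article*

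**What the plan says.** All places are in the protocol article.

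**Hypotheses.** Hypothesis 2 describes effects of the mindfulness arm (MBI) "in which the beneficial effects on insomnia severity will be mediated by rumination and psychological function". Hypothesis 3 describes effects of the Tai Chi arm (TCC) "in which the promising effects on insomnia severity will be mediated by the arousal level and physical function". Hypothesis 4 reads: "The favourable effects of the MBTCC group on insomnia severity will be mediated by all the proposed mediators". No moderator appears in any of them, nor in aims 2 to 4 under Study aims. Hypothesis 2 also contains an arm comparison with sleep hygiene education (SHE): "Participants in the MBI-alone group will experience significantly greater improvements than those in the SHE control group in the primary outcomes across time". Hypothesis 3 makes the same comparison for TCC.

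**Data processing and analysis.** For hypotheses 2 to 4, "macro PROCESS SPSS and the bootstrapping approach will be used to assess the moderated mediation effects in the path model". The next sentence is "Each mediator will be mean centred to form the interaction terms"; the other variable in the product is not named. Age and gender are given as examples of covariates. The method is then described: "The PROCESS macro is based on ordinary least squares regression". The paragraph ends by counting hypotheses 2 to 4 as supported if there is any mediation effect. The linear mixed model is introduced as the test of the first hypothesis. The section opens with "The data will be analysed using SPSS version 26.0 on an intention-to-treat basis", and the Discussion adds that all outcome data obtained are analysed whatever the adherence.

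The article does not say which visits supply the mediator and the outcome, how the four visits are laid out in the path model, or how missing values are treated there.

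**The concern.** Hypothesis, test and decision rule describe three different things. The hypotheses say that an indirect effect exists. The test named is for whether an indirect effect changes with a third variable. The rule goes back to existence, in a form too weak for hypothesis 4. Two analysts could follow the text faithfully, report different quantities and reach opposite conclusions, and the choice could be made after seeing the data.

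Secondly, hypotheses 2 and 3 claim superiority over SHE across time, yet the only method assigned to them is an ordinary least-squares path model. Such a model does not by itself account for repeated measurements, and it does not by itself use partly observed participants. The likelihood-based mixed model does both.

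At stake is what aims 2 to 4, three of the five study aims, can conclude about mechanism, together with two of the trial's comparisons with control.

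**Working it through.** **1. The plan's own figures.** Sample size gives 180 evaluable participants and 30% attrition: 180 / 0.70 = 257.1, against 256 stated (256 x 0.70 = 179.2). The power figures there are for a main effect and an interaction. No figure is given for the mediation tests, so there is none to reproduce on this point.

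**2. Hypothesis, test and rule side by side.**

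| | Mechanism claimed | Test assigned | Counted as supported if |
|---|---|---|---|
| H2 | MBI vs SHE, through rumination and psychological function | moderated mediation, moderator unnamed | any mediation effect |
| H3 | TCC vs SHE, through arousal and physical function | same | same |
| H4 | MBTCC (comparator not named), through all proposed mediators | same | same |

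**3. What each test targets.** Let X be arm, M mediator, Y insomnia severity (ISI) and W the unnamed second variable.
- Simple mediation: M = aX + error; Y = c'X + bM + error. The indirect effect is a x b. This is what the hypotheses describe.
- With a mediator interaction: Y = c'X + b1·M + b3·(M x W) + error, plus a main effect of W if W is not arm. The indirect effect becomes a x (b1 + b3·W), and moderated mediation is tested through a x b3.
- If mediation is real and does not vary, b3 = 0. Then a x b3 = 0 while a x b is not. With a = 0.5 and b = 0.4, a x b = 0.20 and a x b3 = 0.

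**4. Illustration.** Assumed: a = 0.5, b = 0.4, no moderation, W = arm, percentile bootstrap, 200 runs. If a is read in SD units, it is close in size to the pilot's rumination effect for MBI vs SHE in Table 1 (-0.51).

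| | n = 128 (two full arms) | n = 90 |
|---|---|---|
| Simple indirect effect detected | 75.5% | 58% |
| Product a x b3 detected | 4.5% | 3% |

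The Monte Carlo standard error of the first figure is sqrt(0.755 x 0.245 / 200) = 0.03. The contrast between the rows matters, not the exact values.

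**5. The rule for hypothesis 4.** The Mediators section yields four candidates: SF-12 physical, SF-12 mental, rumination and hyperarousal. Under the stated rule, one of the four is enough to support a claim about all four. If each were tested at 5%, the tests were independent and no mediator truly worked, the chance of at least one positive would be 1 - 0.95^4 = 0.185. A rule that requires all four could not exceed 0.05.

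**6. The arm comparisons.** The mixed model is tied to hypothesis 1 and PROCESS to hypotheses 2 to 4. Read literally, MBI vs SHE and TCC vs SHE across time have no repeated-measures test.

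**7. Figures that depend on an unstated layout.**
- One row per person, complete cases only, with the full 30% lost at the visits used: 128 x 0.70 = 89.6, about 90 per active-vs-SHE contrast.
- Three follow-up rows per person stacked as independent, with within-person correlation assumed at 0.3, 0.5 or 0.7: variance of the arm-to-mediator path understated by 1 + 2ρ = 1.6, 2.0 or 2.4, so the SE is too small by a factor of 1.26, 1.41 or 1.55.

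These belong to different layouts and cannot be added. The article commits to neither.

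**The case against.** The strongest reply is that the plan does aim at mediation: the closing rule speaks of a mediation effect, and a further sentence says the mediating effect will also be examined graphically. If the unnamed second variable is arm, conditional indirect effects can be derived from the model, and these bear on hypotheses 2 to 4. This stands in part. It is why the supportable statement is that the target is undefined and unmatched, not that the analysis must yield the wrong quantity. It does not remove the mismatch, because the text names neither the second variable nor the quantity to be reported.

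Three stronger readings are tempting, and the document supports none of them.
- A reader might infer that incomplete participants are dropped. The article does not say so. The Discussion says that all outcome data obtained are included, and imputation before least squares is compatible with the text and may be set out in the full protocol or SAP.
- A reader might infer that visits are stacked as independent rows. No layout is stated; a single visit or a change score fits equally well.
- A reader might infer that baseline ISI and baseline mediators are left out of the model. The covariates are given as examples, so they are not excluded.

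It can also be said that the mixed model for hypothesis 1 will contain all four arms, so the comparisons with SHE can be read from it. That is true, and it makes the repair nearly free, but the text does not assign them there. Finally, aims 2 to 4 are worded as exploratory and the test of hypothesis 1 is unaffected. That limits the weight of the point without answering it.

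**Conclusion.** The point holds in two parts.

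The first rests on the text alone. Hypotheses 2 to 4 state mediation without a moderator, the analysis section tests moderated mediation with an unnamed second variable, and one lenient rule covers all three hypotheses although hypothesis 4 demands every mediator. The size depends on which quantity is finally reported. Under the simulation's assumptions, a real and constant indirect effect would be found in about three runs in four at n = 128 if the simple effect is tested, and in no more than about 5% of runs if only the moderated product is.

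The second part is narrower. The comparisons with SHE in hypotheses 2 and 3 are routed to a least-squares model, which does not by itself handle repeated or partly observed data, so the intention-to-treat statement is not secured for them. This is a gap between the claim and the assigned method, not evidence that participants are dropped or visits stacked. The 128-to-90 and SE figures are conditional on a layout the article does not state and should not be quoted as the size of the problem.

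The change should be made. It alters what three aims can conclude, but not the primary comparison.

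**What to change.** 1. Delete the moderation wording and the mediator interaction terms from the main test of hypotheses 2 to 4. Alternatively, name the moderator and make that analysis secondary.
2. Define the quantity: the bootstrap indirect effect for each named mediator in each active-vs-SHE contrast, with the comparator for hypothesis 4 stated.
3. Measure the mediator before the outcome, for example mediator at T2 and ISI at a later visit. The exact lag is a design choice, but it should be fixed in advance.
4. Adjust for baseline ISI and the baseline value of each mediator, all collected at T1, as well as age and gender. Randomisation protects the arm-to-mediator path but not the mediator-to-ISI path.
5. Use multiple imputation or a full-information maximum likelihood path model, so that all randomised participants contribute.
6. Test MBI vs SHE and TCC vs SHE across time as contrasts in the mixed model.
7. Write a decision rule for each hypothesis. Hypothesis 4 should require every proposed mediator; hypotheses 2 and 3 should say whether one or both named mediators are needed.

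Cost: revised wording and modest extra analysis work, with no new data. Full-information maximum likelihood would mean replacing PROCESS for this step. A fixed lag misses mediator change that comes later, and a rule requiring all mediators makes hypothesis 4 harder to support.
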